#### Recovery room data collection

Immediately after the examination, the patient is transported to the recovery room until fully awake.

After entering the recovery room, test the MOAA/S score every 5 min and record it.

Record the time required from the end of the operation to the patient’s MOAA/S score recovering to 5 points (need to reach 5 points continuously for three times, choose the first time with a score of 5).

Measure NIBP every 3 min after entering the recovery room and record it.

Continuously monitor SpO_2_ until the end of the examination and record the minimum SpO_2_ during the procedure.

Adverse events occurring in the recovery room (see 1.10), such as SpO_2_ below 90%, positive pressure mask ventilation, jaw support-assisted ventilation, systolic blood pressure < 80 mmHg or the need for vasopressors, systolic blood pressure ≥180 mmHg, *HR* ≤ 55 beats/min, and *HR* > 100 beats/min

When the subjects meet the discharge criteria, record their anesthesia satisfaction score (0–10 points, with 0 indicating very dissatisfied and 10 indicating very satisfied).

Whether flumazenil was used for antagonism in case of delayed awakening.

When the patient’s MOAA/S score recovers to 5 points, use the modified Brice questionnaire to determine if the patient was aware during the procedure.

Collect information on the operator’s years of experience.

#### Postoperative day 1 data collection

Collect pathological data on the first day after the operation, conduct telephone follow-up, and record relevant adverse events.

### Strategies for enhancing participant retention and ensuring comprehensive follow-up {18b}

There is a follow-up period, and it consists of a postoperative follow-up scheduled for one day. Participants will be assessed during this follow-up to monitor their progress and address any immediate concerns.

To promote participant retention and ensure complete follow-up, we have implemented comprehensive strategies. Typically, comprehensive follow-up is ensured by adhering to the recommendations of the anesthesiologist. These include regular communication with participants by telephone. Moreover, a meticulous effort is made to capture as many planned outcomes as possible for all participants, including those who discontinue their involvement in the study.

### Outcomes {12}

All the outcome measurements will take place at the baseline (before treatment) and the first day and second day during treatment (Fig. 4).

**Fig. 4 Fig4:**
[figure not shown]
Study schedule

####  Primary outcome

The success rate of patients in both groups who successfully completed upper gastrointestinal endoscopy and treatment. Success will be evaluated using a composite endpoint index comprising the following criteria: (1) MOAA/S score of ≤ 3 points before endoscope insertion into the oral cavity, (2) no interruption of endoscopic examination due to inadequate sedation, (3) no occurrence of SpO_2_ < 90% during the examination, (4) no incidence of systolic blood pressure < 80 mmHg, systolic blood pressure ≥ 180 mmHg, heart rate (HR) ≤ 55 beats/minute, or *HR* > 100 beats/minute during the examination.

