**Methods:**

A total of 576 high-risk patients scheduled to undergo upper gastrointestinal endoscopy are planned to be enrolled in this study and randomly allocated to either the remimazolam or propofol group. The primary outcome measure is a composite endpoint, which includes (1) achieving a Modified Observer’s Alertness/Sedation scale (MOAA/S) score ≤ 3 before endoscope insertion, (2) successful completion of the endoscopic procedure, (3) the absence of significant respiratory instability during the endoscopy and treatment, and (4) the absence of significant circulatory instability during the examination. The noninferiority margin was 10%. Any adverse events (AEs) that occur will be reported.

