### Interventions {11a}

Upon obtaining signed informed consent from the subject, the following process is executed (Figs. 2 and 3):Screening periodAfter the patient enters the endoscopy examination room and decides to undergo upper gastrointestinal endoscopy treatment, the researcher collects information on the patient’s demographics, medical condition, and proposed examination plan. An independent anesthesiologist evaluates the patient’s examination plan before randomization, and eligible patients are selected based on the inclusion/exclusion criteria. Patients should be assessed by researchers who are knowledgeable about the protocol and authorized to do so in a quiet environment. The study’s purpose, methods, potential benefits, and risks must be thoroughly explained to the patient and/or their representative, and data collection and follow-up procedures before, during, and after the examination must be detailed.The researchers should address the patient and their family members’ questions in detail, allowing sufficient time for consideration and obtaining informed consent from the patient and/or their representative on a completely voluntary basis. The assessor must not be involved in the patient’s examination, sedation, or anesthesia management plan. *Sedation management plan*: An anesthetist with the title of attending physician or above will implement the sedation and anesthesia plan. The patient enters the endoscopy consultation room’s preparation area and takes 10 g of lidocaine gel (containing 0.2 g of lidocaine) orally 5 min before the examination. The patient assumes a left lateral position on the treatment bed in the endoscopy consultation room, and basic vital signs including noninvasive blood pressure (NIBP) of the right upper arm, electrocardiogram, and pulse oxygen saturation (SpO_2_) are monitored. Oxygen is continuously administered through a 4L/min nasal cannula throughout the procedure until the patient fully awakens. A venous line is established, and sufentanil 5 μg is administered intravenously. Patients scheduled for upper gastrointestinal endoscopy are randomized to receive one of two sedative drug infusions: propofol in group C or remimazolam in group R. In group C, patients receive a single dose of propofol at 1.5 mg/kg, while in group R, patients receive a single dose of remimazolam at 0.15 mg/kg, both administered within 1 min. According to the domestic expert consensus, moderate or deep sedation is required for upper gastrointestinal endoscopic examination. Therefore, the MOAA/S score (Appendix 2) should be assessed 1 min after propofol injection. If the MOAA/S score is greater than 3 points, propofol 0.5 mg/kg or remimazolam 0.05 mg/kg should be administered repeatedly until the MOAA/S score is less than or equal to 3 points, with a maximum of five repetitions. The VAS (Appendix 3) should be assessed during propofol or remimazolam injection.*Intraoperative monitoring*: Intraoperative monitoring includes electrocardiogram, noninvasive blood pressure, pulse oxygen saturation, and, when necessary, body temperature, urine output, end-tidal carbon dioxide concentration, and blood glucose levels.*Sedation maintenance plan*: During the examination procedure, the chief anesthesiologist determines whether to administer additional trial medication based on the surgical process and duration. Propofol (0.5 mg/kg) or remimazolam (0.05 mg/kg) is administered in single doses with a minimum interval of 1 min to maintain the patient at an appropriate level of sedation (MOAA/S score ≤ 3). If sedatives are insufficient to maintain appropriate sedation during the examination, the investigator may decide to use alternative sedative agents (midazolam).*Examination plan*: Based on the type of lesion, the endoscopic examination of the upper digestive tract in our hospital may include, but is not limited to, upper gastrointestinal inflammation, tumors, ulcers, polyps, gastroesophageal varices, and gastrointestinal strictures. According to the type of endoscopic treatment of the upper gastrointestinal tract, it may include, but is not limited to, sclerotherapy, argon plasma coagulation, high-frequency electrocautery, and submucosal dissection. Various procedures are conducted following established clinical surgical protocols. *Postoperative management plan*: After the examination or procedure, the patient enters the anesthesia recovery room, where continuous monitoring of ECG, noninvasive blood pressure, and oxygen saturation occurs. The MOAA/S score is assessed every 5 min. Once the score reaches 5 points for three consecutive assessments, and blood pressure, heart rate, and oxygen saturation are normal and stable, the patient can leave the recovery room accompanied by a companion. In case of special circumstances, refer to the adverse event handling procedures.

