#### Intraoperative data collection

Starting from the administration of intervention drugs, test the MOAA/S score every 30 s for 5 min, and then test every 2 min until the examination and operation are completed.

Record the time interval (seconds) from the start of intervention drugs to the time when MOAA/S score ≤ 3.

Record the presence of injection pain during the administration of intervention drugs using a visual analog scale (VAS) ranging from 0 to 10, where 0 indicates no pain and 10 indicates maximum pain (see Appendix 3). This assessment is conducted 1 min and 20 min after the start of drug administration or every 5 min thereafter if the patient remains sedated until the patient can complete the scale.

Record the MOAA/S score when the endoscope is smoothly placed in the esophagus.

Record the dose of intervention drugs used when the endoscope is smoothly inserted into the esophagus (including additional and rescue drugs, types, frequency, and dosage).

Measure NIBP every 3 min from the start of intervention drugs until the end of the examination.

Continuously monitor SpO_2_ until the end of the examination and record the minimum SpO_2_ during the procedure.

Record the total duration of the examination and operation (in minutes).

Record the types, frequency, and dosage of additional or rescue drugs during the examination, along with the corresponding time points.

Record the number of interruptions during the examination and the reasons for interruption, along with the time elapsed since drug administration began.

Record adverse events and their corresponding times during the period from drug administration to the end of the examination (see 1.10), such as respiratory spasms, reflux aspiration, coughing during endoscope entry into the oral cavity, SpO_2_ below 90% due to repeated coughing, SpO_2_ below 90% due to respiratory depression, positive pressure mask ventilation, jaw support-assisted ventilation, systolic blood pressure < 80 mmHg, or the need for vasopressors, systolic blood pressure ≥ 180 mmHg, *HR* ≤ 55 beats/min, *HR* > 100 beats/min, and the frequency and conditions of severe arrhythmias.

Operator satisfaction score (0–10 points, with 0 indicating very dissatisfied and 10 indicating very satisfied).

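### The primary composite and its two-condition sensitivity version do not score rescue midazolam, so a patient in whom the allocated sedative failed can count as a success for that drug

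*Protocol article*

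**What the plan says.** All references are to the protocol article.

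- **Primary outcome.** Success needs MOAA/S at or below 3 before the endoscope goes in, then "no interruption of endoscopic examination due to inadequate sedation", then "no occurrence of SpO_2_ < 90% during the examination", then systolic pressure and heart rate within stated limits. No criterion mentions a drug other than the allocated one.
- **Interventions {11a}, sedation maintenance plan.** When the sedatives do not keep the patient at the intended level, "the investigator may decide to use alternative sedative agents (midazolam").
- **Secondary outcomes.** The type, frequency and dose of remedial drugs form sedation efficacy item 6. Airway intervention is safety item 4.
- **Intraoperative data collection.** Additional and rescue drugs are recorded with their times. So are "positive pressure mask ventilation, jaw support-assisted ventilation" and systolic pressure below 80 mmHg "or the need for vasopressors".
- **Sensitivity analysis {20c}.** The success definition is relaxed to two conditions: the MOAA/S criterion and no sedation-related interruption. A per-protocol analysis is added.
- **Abstract, Methods.** Component 2 reads "successful completion of the endoscopic procedure". The Primary outcome section words it as absence of interruption for inadequate sedation, although its opening sentence also speaks of patients who completed the procedure.

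**The concern.** The trial asks whether remimazolam sedates high-risk patients no worse than propofol. The need for a different sedative is direct evidence that the allocated drug was not enough, but the primary composite ignores it. In a superiority trial, unscored rescue usually hides a benefit. In a non-inferiority trial it can hide a deficit, because an arm that needs more rescue is pulled towards the other arm.

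Rescue is at the investigator's discretion, and under {17a} the interventionists assess outcomes and know the allocation. Its use could therefore differ between arms for reasons other than the drug. None of the planned analyses described in the article counts rescue as failure. The {20c} endpoint keeps only the two components that rescue can satisfy. The per-protocol set does not clearly remove rescued patients, because the protocol permits midazolam.

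A smaller problem sits beside this: component 2 has two wordings, and they can classify the same patient differently.

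**Working it through.** **1. How a rescued patient is scored.** Take a patient who reaches MOAA/S 3 or less on the allocated drug, becomes too lightly sedated during the examination, receives midazolam and finishes without interruption, with SpO2, systolic pressure and heart rate within limits. All four primary criteria are met, and so are both {20c} conditions. The patient is a success in each.

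**2. The plan's own figure.** Inputs from Sample-size calculation {14}: success 79% in both arms, margin 0.10, one-sided alpha 0.025, power 0.80.

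n per arm = (1.960 + 0.842)² × 2 × 0.79 × 0.21 / 0.10² = 260.4, rounded up to 261, or 522 in total. This matches. Adding 10% gives 261 × 1.10 = 287.1, so 288 per arm and 576 in total, as stated.

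**3. What unscored rescue can do.** *Assumptions, not in the protocol:* with rescue scored as failure, true success is 79% on propofol and 69% on remimazolam, which is exactly at the margin. A net excess r of remimazolam patients is rescued and otherwise meets every criterion. Scored as written, remimazolam success becomes 0.69 + r.

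P(claim) = Φ[(0.10 − (0.79 − p_R)) / SE − 1.96], where p_R = 0.69 + r and SE = √[0.79 × 0.21/n + p_R(1 − p_R)/n].

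Worked case, r = 0.05 and n = 261: SE = √[(0.1659 + 0.1924)/261] = 0.0371; 0.05/0.0371 = 1.35; Φ(1.35 − 1.96) = 0.27.

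| Excess rescue r | Observed difference | 261 per arm | 288 per arm |
|---|---|---|---|
| 0 | −10 points | 0.025 | 0.025 |
| 2 points | −8 points | 0.076 | 0.080 |
| 5 points | −5 points | 0.271 | 0.294 |
| 10 points | 0 | 0.801 | 0.838 |

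Exact binomial enumeration with a Wald 95% lower limit agrees with each entry to within 0.001.

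**4. What stricter scoring costs.** If rescue-as-failure lowered success to 74% in both arms (again an assumption): n per arm = 7.849 × 2 × 0.74 × 0.26 / 0.01 = 302.02, rounded up to 303, or 606 evaluable against 522. At 261 per arm, power falls from 0.80 to 0.74.

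**5. Component 2, side by side.**

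| Case | Abstract wording | Primary outcome, criterion 2 |
|---|---|---|
| Interrupted for inadequate sedation, then completed | met | not met |
| Abandoned for another reason | not met | met on its own wording; the section's opening sentence points the other way |

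**The case against.** The case for leaving the endpoint alone has substance.

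- **Direction is not established.** The bias helps remimazolam only if rescue is commoner in that arm. Equal rescue leaves the difference unchanged and mainly affects the success rate and power. More rescue on propofol would work against the claim. This stands, and it is why the table is an illustration.
- **The route is narrow.** Midazolam appears in the maintenance plan, while the induction step names only the trial drugs with a capped number of repeat doses. This mostly stands. However, the data-collection section refers to rescue drugs used by the time of insertion, so the first component is not clearly protected.
- **Rescue will be reported anyway.** It is a secondary outcome. That gives visibility, but it does not change how the non-inferiority decision is made.
- **A treatment-policy reading is possible**, comparing each drug with rescue as needed. The article does not state it.
- **Recruitment is under way** (Trial status {3}), so redefining the primary endpoint has a price. This stands and shapes the fix.

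A reader might infer that leaving out vasopressor use and airway support is the same flaw. The protocol does not support that. Such patients succeed only if systolic pressure and SpO2 stay within the limits. These are cardiorespiratory events, not sedation failures, and numeric thresholds are a defensible choice. The Background and Discussion name propofol as the drug that depresses respiration and circulation, so their omission may well count against remimazolam. A reader might also infer that the abstract and outcome section flatly contradict each other. Because the outcome section opens with completion, the clear conflict is confined to examinations interrupted for inadequate sedation and then completed.

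**Conclusion.** The point holds for rescue sedation. Applied as written, the primary composite and the {20c} endpoint can both score a failure of the allocated sedative as a success, and no analysis described in the article corrects for it. The size cannot be computed from the protocol, because no rescue rate is given. The probabilities in the table rest on three assumptions: a strict difference exactly at the margin, a net rescue excess on remimazolam, and rescued patients who meet every other criterion. They show that the scoring rule could decide the conclusion, not that it will. The 10-point case is the extreme one; an excess of 2 points takes the false-claim rate from 2.5% to about 8%. The component 2 discrepancy is real but is mainly a matter of wording.

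**What to change.** Before the analysis, and without changing who receives rescue:

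1. Score any non-allocated sedative given before the end of the procedure as failure, in the primary composite and in the {20c} endpoint. Keep the present definition as a sensitivity analysis.
2. If the sponsor prefers not to change the primary endpoint mid-trial, pre-specify the rescue-as-failure version as a key sensitivity analysis that must agree before non-inferiority is claimed.
3. Use one wording for component 2 in the Abstract, the Primary outcome section and {20c}. State how an examination interrupted for inadequate sedation and then completed, and one abandoned for another reason, are scored.
4. Leave vasopressor use and airway support out of the primary. Report a supplementary composite that includes them.

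**Cost.** Rescue drugs, airway support and vasopressor need are already collected, so no new data are required; the changes are to the protocol, analysis plan and registry wording, with the ethics approval that {25} requires for amendments. The downside should be stated openly: success will be lower than 79% if rescue occurs, and power will fall. At 74% in both arms the requirement of 606 evaluable patients would exceed the 576 planned for enrolment.

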#### Secondary outcomes

*Sedation efficacy outcomes*: (1) MOAA/S score after single administration; (2) time required to achieve a MOAA/S score of ≤ 3 points following single administration; (3) for patients not achieving adequate sedation depth after a single dose and documentation of additional medication doses and frequency; (4) total amount and number of additional administrations of remimazolam or propofol in both groups during the entire course of upper gastrointestinal endoscopy and treatment; (5) duration from the initiation of medication injection to the completion of upper gastrointestinal endoscopy and treatment; (6) type, frequency, and dose of alternative or additional remedial drugs required when the upper limit of supplementary dosage is exceeded; and (7) operator satisfaction.

*Consciousness recovery outcomes*: (1) Time to full awakening; (2) use of sedative antagonist flumazenil, if applicable; (3) assessment of patients’ recall of upper gastrointestinal endoscopy and treatment process using the Brice questionnaire (Appendix 4) after awakening; (4) duration of patients’ recovery; and (5) overall patient satisfaction.

*Safety outcomes*: (1) Incidence of hypertension or hypotension during the procedure and in the recovery room, (2) incidence of tachycardia or bradycardia during the procedure and in the recovery room, (3) incidence of low oxygen saturation during the procedure and in the recovery room, (4) airway intervention rate during the procedure and in the recovery room, (5) incidence of coughing within 1 min after endoscope insertion, (6) incidence of coughing during upper gastrointestinal endoscopy and treatment, and (7) incidence of injection-related pain.

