### Sample-size calculation {14}

The study plans to enroll 576 patients. The basis for sample size calculation is as follows: According to the literature report [7], patients undergoing upper gastrointestinal endoscopy and treatment with propofol sedation had a completion rate without sedation-related complications of 79%. Using a two-sample *z*-test for proportions to assess the primary outcome measure, the estimated non-inferiority margin is an absolute difference of 10% for the primary outcome measure. Setting a non-inferiority difference value of 0.1, a power (1-β) of 0.8, and a one-sided α of 0.025, a total sample size of 522 cases is required for the calculation. Accounting for an anticipated loss to follow-up rate of 10%, the total sample size is 576 cases (288 participants per group).

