#### Efficacy evaluation{20a}

Primary endpoint evaluation: In the intention-to-treat (ITT) analysis population, a chi-square test will be used to compare the success rates of patients completing endoscopic examination and treatment between the two groups. Simultaneously, a generalized linear model will be employed to calculate the unadjusted and adjusted absolute risk differences (ARD). Adjusted variables will encompass stratification indicators (invasive procedures during upper gastrointestinal endoscopy and treatment), BMI, age, concurrent respiratory diseases, concurrent cardiovascular and cerebrovascular diseases, liver and kidney function abnormalities, and operator experience. Secondary effect sizes will be presented as odds ratios (OR) with a 95% confidence interval.

Evaluation of secondary endpoints: For the intention to treat (ITT, includes all participants who were randomly assigned, regardless of whether they completed the entire study or fully adhered to the study protocol) population, chi-square test or *t*-test will be employed for comparative analysis based on variable nature (e.g., categorical variables like low oxygen saturation, hypotension, tachycardia, intraoperative awareness, recovery delay, or continuous variables such as MOAA/S, NIBP, HR, and SpO_2_). Results will be reported as odds ratios (OR) and 95% confidence intervals using a generalized linear model. Time event variables (e.g., time to achieve a MOAA/S score of ≤ 3 points after a single dose) will be analyzed using Cox regression to describe and compare the two groups, generate Kaplan-Meier curves, express results as hazard ratios (HR), and report a 95% confidence interval.

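### Secondary sedation outcome (3) covers additional doses only in patients whose first dose was insufficient, a subset formed after randomisation, while the plan tests secondary endpoints in all randomised patients

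*Protocol article*

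**What the plan says.** In the protocol article, under Secondary outcomes, item (3) of the sedation efficacy list reads "for patients not achieving adequate sedation depth after a single dose and documentation of additional medication doses and frequency". Item (4) is the "total amount and number of additional administrations of remimazolam or propofol in both groups during the entire course" of endoscopy and treatment.

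Interventions {11a} shows how a patient comes under item (3): "If the MOAA/S score is greater than 3 points, propofol 0.5 mg/kg or remimazolam 0.05 mg/kg should be administered repeatedly" until the score is 3 or below, "with a maximum of five repetitions". Later doses follow another rule: during the procedure, "the chief anesthesiologist determines whether to administer additional trial medication based on the surgical process and duration".

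Efficacy evaluation {20a} sets the population for secondary endpoints as intention to treat, which "includes all participants who were randomly assigned, regardless of whether they completed the entire study or fully adhered to the study protocol". It adds that a "chi-square test or *t*-test will be employed for comparative analysis based on variable nature". Item (3) is not exempted, and no sentence says what value a patient takes when the first dose was enough.

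The intraoperative part of Data Collection {18a} records the drug dose used by the time the endoscope is in the esophagus, with additional and rescue drugs and their frequency. That record is not limited to any subset.

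**The concern.** A MOAA/S score above 3 after the first dose is a response to the allocated drug. If one first dose works more often than the other, the patients left in item (3) are a different selection in each arm. The arm whose first dose works more often may leave only its hardest patients, while the other arm also leaves many who need just one more dose. Comparing top-ups between those groups asks how difficult each drug's non-responders were. It does not ask how much topping-up each drug required in the patients randomised to it.

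Item (4) covers all patients, but it adds maintenance doses, given at the anesthesiologist's discretion and dependent on procedure length, to the induction top-ups. The induction requirement is therefore isolated only in item (3), where the population is selected.

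**Working it through.** **The plan's own figures.** The documents state no figure for item (3). The only sizing figure is for the primary outcome: 7.849 × 2 × 0.79 × 0.21 / 0.10² = 260.4, so 261 per arm and 522 in total. Then 261 × 1.10 = 287.1, so 288 per arm and 576 in total. Both reproduce, and neither bears on this point except to give 288 per arm.

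**Inputs from the documents.** A top-up is one third of the first dose in both arms (0.5/1.5 and 0.05/0.15). The cap is five top-ups. There are 288 patients per arm.

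**Inputs assumed.** First-dose failure proportions and the number of top-ups per failure are assumptions throughout.

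**Formula.** Let f be the proportion whose first dose fails and m the mean top-ups per failure. The subset comparison sets m_A against m_B. The comparison over all randomised patients sets f_A·m_A against f_B·m_B. If arm A has more failures, the order reverses when 1 < m_B/m_A < f_A/f_B.

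**Illustration 1: constant chance q of needing a further top-up, capped at five.** Then m = (1 − q⁵)/(1 − q), which gives 1.25 for q = 0.2, 1.43 for q = 0.3 and 1.94 for q = 0.5.

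| Assumed (A vs B) | Per failure | Per randomised patient |
|---|---|---|
| f 40% vs 10%, q 0.3 in both | 1.43 vs 1.43 | 0.57 vs 0.14 |
| f 30% vs 10%, q 0.2 vs 0.5 | 1.25 vs 1.94 | 0.375 vs 0.19 |

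In the first row a four-fold difference disappears. In the second the order reverses. In 4,000 simulated trials with the second row's inputs, a t-test in the subset was significant in the reversed direction in about 96% of runs (88% with Welch's version). That frequency follows from inputs chosen to produce the reversal.

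**Illustration 2: direct arithmetic on f and m.**
- 40% × 1.25 = 0.50 against 10% × 2.0 = 0.20: reversed.
- 20% × 1.4 = 0.28 against 10% × 1.6 = 0.16: reversed.
- 15% × 1.2 = 0.18 against 10% × 2.0 = 0.20: not reversed, but the subset exaggerates a small difference.

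**Illustration 3: each patient has a dose need, with the first dose as 1 unit.** The number of top-ups is the number of one-third units needed beyond 1, capped at five. The stronger arm's need is shifted down by 0.3.

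| Dose need | Arm | Failures | Per failure | Per patient |
|---|---|---|---|---|
| Normal (mean 0.9, SD 0.3) | weaker | 37% | 1.22 | 0.45 |
| | stronger | 9% | 1.08 | 0.10 |
| 5% hard to sedate in both arms (mean 2.0, SD 0.3), the rest mean 0.9, SD 0.2 | weaker | 34% | 1.40 | 0.48 |
| | stronger | 7% | 2.73 | 0.20 |

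In the mixture the shift applies only to the patients who are not hard to sedate. With the plain normal need the direction is preserved, but the ratio shrinks from about 4.5 to 1.1. With the mixture the order reverses.

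**The case against.** The best defence is that the wording fixes no defect. By design, a patient whose first dose sufficed has no induction top-ups, so naming only those who can have them loses no events. The distortion arises only if someone divides by the number of failures and tests the result. Item (3) states neither a denominator nor a test. Its grammar is broken, and it speaks of documentation, which fits a descriptive table. The examples of tested variables under Efficacy evaluation do not include top-up counts. Such detail is often settled in a fuller plan, which is not shown here.

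Much of this stands. A reader might infer that the definition cannot be analysed by intention to treat at all. That goes too far, because scoring zero for first-dose successes would deliver that set. A reader might also infer that the trial is certain to run a subset test. The documents do not say so.

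What remains is that item (3) is listed as a secondary efficacy outcome, it names a post-randomisation subset, and the testing rule for secondary endpoints is general and exempts nothing. The two statements do not fit together as printed. Item (4) does not fill the gap, because it pools induction with maintenance doses.

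**Conclusion.** The point holds as a flaw in the definition of one of 19 secondary outcomes. If item (3) is tested in the subset it names, the comparison is not randomised. It can understate, hide or reverse the difference in induction top-ups.

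A reader might conclude that the trial's efficacy message would come out backwards. The documents do not support that. Reversal needs the ratio condition above, for example a small hard-to-sedate group in both arms, and it does not occur under a plain normal dose need. No failure rates or top-up distributions are given, so every size shown is an illustration. Items (1) and (2) describe the response to the first dose, and item (4) counts all additional doses in both groups, so a large difference in first-dose failure would be visible to anyone reading them together. The primary outcome, margin and sample size are unaffected, and no dosing rule is in question. This is a low-severity point with an almost free remedy.

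**What to change.** Reword item (3) as the number and dose of induction top-ups given before endoscope insertion in all randomised patients, zero where the first dose sufficed. Report the proportion of first-dose failures by arm alongside it. Compare the arms with a count or ordinal model, or a rank test, that accounts for the randomisation stratum (planned invasive treatment); many zeros and a cap of five make a t-test a poor choice. Keep any figures restricted to first-dose failures as a table labelled descriptive and untested. If item (3) was only ever meant as description, state that and exempt it from the testing rule under Efficacy evaluation.

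The cost is one definition line and one sentence of analysis. Doses and their frequency up to insertion are already to be recorded under Data Collection for every patient, so no new data are needed and no procedure changes.
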